### Interim analyses {21b}

Interim analyses will be performed with the data of the midterm survey using the same statistics as in the final analyses. All members of the project will have access to these results and will participate in making the final decision to terminate the intervention.

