#### 12.4 Time points

Hospital days will be sourced from the register data of the health insurance companies. These data are updated continuously. The collaborating health insurance companies will provide these data for evaluation after the intervention retrospectively to the point in time 1 year prior to the start of the intervention. The change scores for hospital days will be computed by subtracting the number of hospital days in the year directly before intervention start from the number of hospital days in the year directly before the end of the regular intervention, i.e. directly before month 18 after intervention start. Data for the secondary outcomes will be collected via a questionnaire (1) at enrolment (baseline survey), (2) 9 months after the start of the intervention (midterm survey), (3) 18 months after the start of the intervention (end survey) and (4) 27 months after the start of the intervention (follow-up survey). The baseline survey will be performed before the study participants have been informed about their assignment to one of the two study conditions. For the questionnaire variables, the core evaluation of the intervention will be based on the change scores between the values of the baseline survey and the values of the end survey, i.e. the survey at month 18 after intervention start.

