### Sample size {14}

The most important analysis in the evaluation addresses the effect of the intervention on the primary outcome, i.e. the number of hospital days. As mentioned above, intervention and waiting control group will be compared with regard to the change scores of hospital days. These change scores will be computed by subtracting numbers of hospital stays 1 year before intervention start from numbers of hospital stays 1 year before the intervention end. The comparison of change scores will be performed using a *t*-test for independent samples. The sample size has been determined with regard to this test. The basic demand was that the test should be able to detect an effect of size 0.2 with a significance level of 0.05 and a power of 0.8. An effect size of 0.2 is a small effect according to Cohen [39]. However, unpublished analyses of our own with numbers of hospital days indicate that the standard deviation of change scores of hospital days will be between 5 and 10. In this case, an effect size of 0.2 would correspond to differences of one to two hospital days. Even a difference of only one day would mean a substantial difference in costs.

Further conditions presupposed for determining the sample are:
Two percent of the included persons could die during the intervention period or withdraw their consent for their data to be used.There could be a dropout rate of 15% in the intervention group and 20% in the waiting control group. The reason for this assumption is that up to 50% of the sample might consist of persons who are not ensured at AOK RH or BARMER. For these persons, the numbers of hospital days will not be provided directly by the health insurance companies. Instead, the patients will have to request the data from their health insurance companies and then transfer them to the project team. Several patients will not do this, with patients in the waiting control group being more likely not to do this. Within this sub-sample, a dropout rate of 30% in the intervention group and 40% in the waiting control group seems realistic. This would correspond to dropout rates of 15% and 20% in the total sample.The allocation ratio of intervention to control is 6:7.The sample size should be divisible by 13 because of the allocation ratio.

All these considerations imply a sample size of 1001.

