## Dissemination plans {31a}

The results of the midterm analyses as well as the results of the final analyses will be submitted for publication in peer-reviewed international scientific journals.

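### All project members see the month-9 between-arm results and share the decision to terminate the intervention, with no criterion, no primary outcome data and no role for the DMC

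*Protocol article*

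**What the plan says.** The section Interim analyses {21b} of the protocol article has two sentences. On method: "Interim analyses will be performed with the data of the midterm survey using the same statistics as in the final analyses". On access and decision: "All members of the project will have access to these results and will participate in making the final decision to terminate the intervention". It gives no significance level, no boundary and no reason for which the intervention might be terminated.

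Section 12.4 Time points places the midterm survey at month 9. On the surveys it states: "Data for the secondary outcomes will be collected via a questionnaire". On hospital days, the primary outcome, it states: "The collaborating health insurance companies will provide these data for evaluation after the intervention retrospectively". It bases the core evaluation of the questionnaire variables on the change from baseline to month 18.

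Other sections bear on the point:
- **Statistical methods {20a}:** if the primary test is not significant, an analysis of variance on all secondary variables decides whether the intervention is effective. The section also expects that effects may show in the mediating variables before they show in hospital days.
- **Who will be blinded {17a}:** there is no blinding, analysts included.
- **Data monitoring committee {21a}:** a committee of people outside the project oversees conduct and safety. The interim analysis is not among its tasks.
- **Dissemination plans {31a}:** "The results of the midterm analyses as well as the results of the final analyses will be submitted for publication" (no date is given).

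**The concern.** Three features combine badly.

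1. **Who sees the results.** Read plainly, all project members include the telephone coaches, who are employed by a partner institution, and the units that mail, collect and enter the questionnaires. In an open-label trial with self-reported secondary outcomes, they would know the arm differences halfway through. Delivery and month-18 answers could shift in response, and those answers can carry the effectiveness verdict.

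2. **What the decision rests on.** Only questionnaire scores exist at month 9. The protocol's own reasoning is that hospital days may respond later than these scores, so the scores cannot settle the primary hypothesis. Terminating on them would cut short the exposure that the primary outcome is meant to reflect.

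3. **What the result may be used for.** The composite compared at month 9 is the one that may decide effectiveness at month 18. Nothing says whether a favourable early result could support a claim.

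**Working it through.** **What a month-9 decision can use**

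- Primary outcome year (section 12.4): the year ending at month 18, so months 6 to 18.
- If the intervention stopped at month 9, exposure inside that window would run from month 6 to month 9: 9 − 6 = 3 of 12 months. Total exposure would be 9 of 18 months.
- Hospital days available at month 9: none, since the insurers deliver them after the intervention.

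**Which significance level the plan works with**

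The only level in the document is in Sample size {14}: "the test should be able to detect an effect of size 0.2 with a significance level of 0.05 and a power of 0.8". Sidedness is not stated, so I checked it against the planned 1001.

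- Inputs: standardised effect 0.2, allocation 6:7, 2% death or data withdrawal, dropout 15% (intervention) and 20% (control).
- Randomised at 1001: 462 and 539. Evaluable: 462 × 0.98 × 0.85 = 384.8 and 539 × 0.98 × 0.80 = 422.6.
- Two-sample t-test, two-sided 0.05: power 0.809 at 1001. The smallest multiple of 13 that reaches 0.80 is 988.
- One-sided 0.05: the smallest multiple of 13 is 780, which does not fit.

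The plan is therefore consistent with two-sided 0.05, that is 2.5% in the favourable direction. This level is set for the primary t-test. Carrying it over to month 9 is an assumption.

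**Error rate of the composite if tested at 0.05 at months 9 and 18**

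Let Z1 and Z2 be the composite test statistics at the two months, standard bivariate normal under no effect, with correlation ρ. The documents do not give ρ, so a range is shown.

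- Two-sided: 1 − P(|Z1| < 1.96 and |Z2| < 1.96)
- Favourable direction only: 1 − P(Z1 < 1.96 and Z2 < 1.96)

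| ρ (assumed) | Two-sided | Favourable direction |
|---|---|---|
| 0.5 | 1 − 0.9093 = 9.1% | 1 − 0.9546 = 4.5% |
| 0.6 | 1 − 0.9125 = 8.8% | 1 − 0.9562 = 4.4% |
| 0.71 | 1 − 0.9169 = 8.3% | 1 − 0.9584 = 4.2% |
| 0.8 | 1 − 0.9219 = 7.8% | 1 − 0.9610 = 3.9% |

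The reference values are 5% and 2.5%. These figures apply only if a favourable month-9 result may support an effectiveness claim.

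**Keeping the month-18 rule separate**

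The rule that either the primary test or the composite can establish effectiveness inflates error without any interim look. I simulated three tests at |Z| > 1.96, assuming a correlation of 0.2 between the primary and the month-18 composite, and 0.1 between the primary and the month-9 composite.

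- Month-18 rule alone: about 9.6% two-sided, 4.8% favourable.
- With the month-9 look added (ρ from 0.8 to 0.5): 12.3% to 13.5% two-sided, 6.2% to 6.8% favourable.
- Share due to the interim: 12.3 − 9.6 = 2.7 to 13.5 − 9.6 = 3.9 points two-sided; 6.2 − 4.8 = 1.4 to 6.8 − 4.8 = 2.0 points favourable.

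**The case against.** A reader might infer four stronger things that the document does not support.

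- **That the month-9 test is run at the full 5% level.** The section refers to the same statistics and names no level. Boundaries are commonly left to an analysis plan, which is not shown.
- **That the interim look necessarily inflates the verdict's error rate.** The core evaluation is tied to month 18, and the fallback applies only after a non-significant primary result, which cannot exist at month 9. The primary test spends no alpha early, and a stop for futility or harm inflates nothing. Setting 12% to 14% against 5% would also charge the interim with inflation that comes mostly from the month-18 rule.
- **That participants will read midterm results before they answer at month 18.** Publication is planned without a date. Early release is possible but not stated.
- **That stopping would leave the primary question with no data.** The sentence concerns the intervention, not data collection. Insurer records could still be obtained, but with truncated exposure.

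The operational risk also has limits. The trial is open-label anyway, so only the aggregate differences would be new knowledge. Questionnaires are postal and double-entered, non-responders get a set sequence of requests, and no extra adherence measures are planned. Much of the primary outcome comes from insurer records.

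These points make the error-rate argument conditional and narrow the routes for bias. They do not answer the governance point. Coaching is tailored to the individual and can shift, the fallback outcomes are self-reported, and the text itself fixes universal access and a shared termination decision without a criterion.

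**Conclusion.** The point stands as a matter of governance and interpretation. As written, everyone in the project sees between-arm results at month 9 and helps decide on termination. They would do so on secondary outcomes alone and without a criterion, while a committee outside the project exists and is not used for this. This rests on the text and needs no assumption about alpha.

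The error-rate part is conditional. It needs testing at 0.05 at both months and a use of the month-9 result that the protocol neither grants nor rules out. Under those assumptions, and for correlations of 0.8 to 0.5, the composite's error rate is 7.8% to 9.1% two-sided, or 3.9% to 4.5% in the favourable direction. The protocol should be changed here, since the bias is avoidable and the remedy is cheap.

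**What to change.** 1. State in Interim analyses {21b} that the month-9 between-arm comparison is non-confirmatory and cannot support an efficacy conclusion or an efficacy or futility stop. If efficacy stopping is kept, pre-specify an alpha-spending boundary for the composite. As an illustration, 0.0052 at month 9 and 0.048 at month 18 give 5.0% overall at a correlation of 0.71 (4.8% to 5.3% for 0.9 to 0.3). This covers the two looks only, not the month-18 primary-or-composite rule.
2. Limit between-arm interim results to the analysts who run them and the existing DMC. The rest of the project sees pooled or process data.
3. Hold publication of between-arm midterm results until the month-18 survey and the hospital data are locked.

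**Cost:** changes of wording, with no new staff and no change to sample size or survey schedule. The analysts remain unblinded, as the protocol already accepts. Midterm publication is delayed by at least about 9 months (18 − 9), and longer if hospital data arrive late, for example from participants who must request their own records. The project team loses early sight of arm differences.

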### Methods for additional analyses (e.g. subgroup analyses) {20b}

A subgroup analysis will be performed with three different groups: (1) the PSG leaders, (2) the common PSG members not receiving telephone-based health coaching and (3) the common PSG members receiving telephone-based health coaching. The data of these subgroups will be analysed in the same way as the data for the total sample. Furthermore, to test whether there are any statistically significant differences between the results for the three groups, regression models will also be computed that refer to all participants but additionally contain terms for the interaction between study condition and subgroup. In the sense of a process evaluation, further analyses will be performed with variables that are only assessed in the intervention group and that are not listed within this protocol. Among other things, these analyses refer to the acceptance of the different intervention components and to the group dynamics within the PSGs.

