**Methods:**

Study participants will be adults enrolled in a DMP for T2DM and/or CHD and living in North Rhine-Westphalia, a state of the Federal Republic of Germany. Study participants will be recruited with the assistance of their general practitioners by the end of June 2021. Evaluation will be performed as a pragmatic randomised controlled trial with one intervention group and one waiting control group. The intervention group will receive the intervention for 18 months. During this time, the waiting control group will continue with usual care and the usual measures of their DMPs. After 18 months, the waiting control group will also receive a shortened intervention. The primary outcome is number of hospital days. In addition, the effects on self-reported health-state, physical activity, nutrition, and eight different psychological variables will be investigated. Differences between values at month 18 and at the beginning will be compared to judge the effectiveness of the intervention.

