### Interventions

#### Explanation for the choice of comparators {6b}

The participants in the control group will receive their usual care together with the DMPs in which they are enrolled. This regimen will be chosen as the comparator because P-SUP is intended as a supplement to DMPs.

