The PSGs will consist of 4 to 6 participants. These will be selected so that their places of residences are as close together as possible. The groups will meet weekly for the full duration of the intervention. As a rule, each meeting will last 90 min. However, the PSGs will be allowed to change the length of the meetings as they see fit. The schedule of the meetings can also be set by the PSGs. As soon as the development of the pandemic allows, the PSGs can choose between face-to-face and digital meetings. The meetings will focus on physical exercise. Individual physical exercises tailored to the abilities / possibilities of the participants will be demonstrated. The selected exercises will address coordination skills, endurance and strength development. Every second month, an external expert will visit the PSG and give a talk on a topic of relevance for people with T2DM and/or CHD. The topics will cover nutrition, medical aspects of the diseases, physical activity, motivation, further psychological aspects of the disease and general aspects of living with a chronic disease.

The telephone-based health coaching will be offered to all participants who score low on the Patient Activation Measure (PAM) [19] and/or low for health literacy (BHLS) [25] before the start of the intervention. Patients will be able to choose whether to accept the offer or not. If the offer is accepted, they will be given motivational interviewing by specially trained staff to compensate for the low levels of activation and/or health literacy. In the first phone call, patients’ intentions and previous experience with regard to physical activity and healthy nutrition will be identified. Based on these intentions and previous experience, the health coaches will then be able to individually address patients’ willingness to change their physical activity and nutritional behaviour during subsequent telephone calls. During these phone calls, various behaviour change techniques [28, 29] will be applied.

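### Splitting common PSG members by receipt of telephone coaching leaves the coached subgroup without controls, so the coaching-by-condition interaction cannot be estimated; the leader contrast can

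*Protocol article*

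**What the plan says.** Section {20b} of the protocol article names three subgroups. The first is the PSG leaders; the others are "2) the common PSG members not receiving telephone-based health coaching and (3) the common PSG members receiving telephone-based health coaching". Two analyses are fixed for them. First, "The data of these subgroups will be analysed in the same way as the data for the total sample", which for hospital days means a t-test of intervention against control (Statistical methods {20a}). Second, "regression models will also be computed that refer to all participants but additionally contain terms for the interaction between study condition and subgroup".

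Coaching is one of the four intervention components (Intervention description {11a}). It is offered to participants with a low PAM and/or low BHLS score before the intervention starts, and "Patients will be able to choose whether to accept the offer or not". The section on adherence {11c} counts it among services not available outside the intervention. For the control arm, the abstract states that "the waiting control group will continue with usual care and the usual measures of their DMPs" during the 18 months, and the section on comparators {6b} says the same. Controls get a shortened programme only afterwards.

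Leader status is a stratification factor (Sequence generation {16a}). The baseline survey is completed before participants learn their allocation (Time points 12.4; Concealment mechanism {16b}).

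**The concern.** Both planned analyses need intervention and control patients in every subgroup. Receipt of coaching cannot supply that: it occurs in one arm only, and among those offered it, it depends on a choice made after randomisation. As written, one subgroup has no comparator. The other is a randomised comparison only if the control patients placed in it are of the same kind as the intervention patients, and no rule for placing controls is given.

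What is at stake is the evidence on patients with low literacy or low activation. The background section gives the lack of special assistance for them as a reason for the programme. The analysts are not blinded (section {17a}), so a placement rule devised once outcome data are in hand would be open to the suspicion that the results shaped it.

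**Working it through.** **1. The plan's own figure.** No number is given for the subgroup analysis. The only related figure is the total of 1001 in Sample size {14}. Inputs there: effect 0.2 SD, significance level 0.05 (taken as two-sided), power 0.8, allocation 6:7, losses of 15% and 20%, and a further 2%.
- Split: 1001 × 6/13 = 462 intervention and 1001 × 7/13 = 539 control.
- Completers: 462 × 0.85 × 0.98 = 384.8 and 539 × 0.80 × 0.98 = 422.6.
- Power of the t-test at these numbers: 0.81. The smallest sufficient total is 978 (982 if the losses are added rather than multiplied), and the next multiple of 13 is 988.

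The stated 1001 is therefore sound and slightly generous. The present point does not touch it.

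**2. Estimability as written.** Code the model with six columns: intercept, arm, leader, coached, arm × leader, arm × coached. During the comparison, coached = 1 occurs only where arm = 1, so arm × coached equals coached in every row. The rank is 5 of 6, confirmed numerically with 462 and 539 participants and low-scorer shares of 20%, 40% and 60%. One of the two interaction degrees of freedom is lost, whatever the sample size. If software drops one of the identical columns, the remaining coefficient is coached minus uncoached common members within the intervention arm, which is not a randomised contrast.

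Leader status is known at randomisation in both arms. Leaders versus all common members pooled is therefore a valid interaction, and the comparison within leaders is intact.

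**3. Uncoached subgroup if it takes all non-leader controls.** Let p be the share of low scorers among common members, u the uptake of coaching among them, and g the difference in mean change between low and other scorers. Assume that decliners resemble other low scorers and that the intervention has no effect.
- Low-scorer share among controls: p.
- Low-scorer share among uncoached intervention patients: p(1−u)/(1−pu).
- Size of the spurious effect: g × [p − p(1−u)/(1−pu)].

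At p = 0.5 and u = 0.4: 0.5 − 0.3/0.8 = 0.125. At p = 0.5 and u = 1: 0.5 − 0 = 0.5.

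| p | u = 40% | u = 60% | u = 80% | u = 100% |
|---|---|---|---|---|
| 20% | 0.07g | 0.11g | 0.15g | 0.20g |
| 50% | 0.125g | 0.21g | 0.33g | 0.50g |

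None of p, u and g is in the protocol. The background section reports low health literacy in more than 50% of the German population, but that is neither this trial's population nor the PAM/BHLS rule. If g were 0.2 SD, the table spans 0.014 to 0.10 SD. The upper end is half the 0.2 SD effect the trial is designed to detect.

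**4. After redefinition by baseline eligibility.** The same six columns, with eligible in place of coached, have rank 6 of 6. For the eligible versus not-eligible interaction, the standard error in SD units is the square root of the sum of 1/n over the four arm-by-eligibility cells. Assumed: leaders are 1/6 to 1/4 of participants and 30-70% of common members score low.
- Leaders 1/6, low 50%: cells of about 160, 160, 176 and 176. SE = √(2/160.4 + 2/176.1) = 0.154. Detectable with 80% power: 2.80 × 0.154 = 0.43 SD. Power for 0.2 SD: Φ(0.2/0.154 − 1.96) = 0.25.
- Leaders 1/4, low 30% or 70%: SE 0.178, detectable 0.50 SD, power 0.20.

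**The case against.** The strongest reply is that receiving coaching is shorthand for being eligible for it. The offer rests on questionnaire scores obtained before the intervention starts, and a regression on all participants makes sense only if the subgroup exists in both arms. An article may also leave the coding of controls to a fuller document. This reading is possible, but it is not what the text says: section {11a} separates the offer from its acceptance, and section {20b} uses receipt. Nor is this a detail left out, because the stated definition and the stated model are incompatible. If eligibility was meant, the wording must still change. The controls' later shortened programme does not help: it comes after the month-18 outcome, and whether it includes coaching is not stated.

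Other parts of the reply stand. A reader might infer that the whole three-group interaction fails; it does not, because leader status is fixed in both arms. A reader might take 0.5g as the size of the bias. That is the full-uptake figure at an assumed p of 50%, and full uptake sits badly with a voluntary offer. A reader might also conclude that the trial can say nothing about low-literacy or low-activation patients. If the baseline scores exist in both arms, the eligibility analysis remains open, though imprecise.

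**Conclusion.** As worded, the coached subgroup has no controls and the coaching-by-condition interaction cannot be estimated. This follows from the protocol's own statements and needs no assumed figure. The leader contrast survives. The uncoached comparison can be computed but is selected if all non-leader controls are placed in it. Its bias is 0.125g to 0.5g at p = 50% and uptake of 40% to 100%, with p, u and g all assumed and decliners taken to resemble other low scorers.

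It would be tempting to treat this as a threat to the trial's main conclusion. The documents do not support that: the analysis is an additional one and enters neither the primary t-test, nor the fallback analysis of variance on the secondary outcomes, nor the sample size. It is a defect in a secondary analysis that should be corrected before outcome data are seen.

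**What to change.** In section {20b}, define the three groups identically in both arms: PSG leaders; common members eligible for coaching (low PAM and/or low BHLS at baseline, with the cut-offs stated); and common members not eligible. Run the within-group comparisons and the condition-by-subgroup interaction on these groups. Report actual receipt of coaching only in the analysis of extent of use already planned in section {20c}, or in the process evaluation. Label the subgroup results exploratory, given power of about 20-25% for a 0.2 SD interaction under the assumed shares.

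Confirm that PAM and BHLS are recorded for controls. The protocol implies this, since the scores precede the intervention and allocation is withheld until the baseline questionnaire is returned, but it does not state it. If so, the cost is a change of wording, with no new data and no change to the sample size.
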